## Abstract

Recruitment remains an issue when conducting randomised controlled trials (RCTs) with a significant proportion of studies failing to reach their target sample size. Studies evaluating interventions to improve recruitment aimed specifically at recruiters to the trial are limited in number. This factorial RCT will evaluate the effectiveness of an educational intervention to trainee principal investigators and a positive reinforcement intervention via an email nudge on increasing recruitment. The targeted recruiters will be in 20 centres nationally recruiting to one large orthopaedic randomised controlled trial, WHiTE 8 COPAL. Centres will be randomised via minimisation to one of four groups. The primary outcome is recruitment rate in the first six months that a centre is actively recruiting, with data being analysed via a Poisson regression model. Results will be presented as adjusted incidence rate ratios with 95% confidence intervals. Secondary outcomes relate to the feasibility and logistics of running the interventions.  We will also collect feedback regarding the educational programme set out for the trainee principal investigators. The study started in August 2018 with the anticipation of the primary objective endpoint by October 2019. The results of this study will be used to inform the design of future RCTs, particularly in orthopaedics in the UK, where the role of Trainee Principal Investigators is now a consistent one across different trials.

**Trial registration:**
11600053, ISRCTN, 20/08/2018;
SWAT 67, Northern Ireland Hub for Trials Methodology Research SWAT repository, 01/10/2017.

## Introduction

Randomised controlled trials (RCTs) are considered the gold standard when evaluating the efficacy and effectiveness of health care interventions. Unfortunately, a significant number of well-designed RCTs struggle with the recruitment of participants and subsequently fail to reach their target sample size
^1^.

Several hypothetical and real-life studies on methods to improve participant recruitment to RCTs have been conducted with mixed results, with only a minority targeting recruiters to the trial
^2–
5^. The results of a survey of clinical trials units in the UK concluded that priorities for evaluation included training site staff, methods of communication with patients and incentivising site staff
^6^.

The aim of this real-life study is to assess the effects of targeting healthcare professional recruiters with an educational intervention with or without positive reinforcement on participant recruitment. This study within a trial (SWAT) will test two different methods of enhancing recruitment: introducing an enhanced trainee principal investigators (TPI) package, and personalised email nudges (see
*Extended data*
^7^) to healthcare professionals involved in patient recruitment. The SWAT will be implemented in a large, UK, multicentre orthopaedic RCT, the WHiTE 8 COPAL trial. The interventions have both been used in current orthopaedic trials, but their effects on recruitment have previously not been investigated.

## Interventions

This will be a multicentre, 2×2 factorial RCT run between August 2018 and October 2019 with random allocation of the recruiting centre to one of four groups:

Group 1: Enhanced TPI package.Group 2: Use of a personalised email nudge to each recruiter.Group 3: Enhanced TPI package and use of a personalised email nudge to each recruiter.Group 4: Usual practice (neither the enhanced TPI nor personalised email nudge).

Full details of each intervention have been provided as
*Extended data*
^7^ and are summarised in
Table 1. The consent to participate as a TPI and interventions will be implemented by the White 8 Research Fellow (author [name]). Consent materials are also available as
*Extended data*
^7^.

**Table 1. T1:** Summary of additional activities in each intervention group.

Activity	Usual practice	Enhanced TPI	Email nudge
Identify TPI for the trial	Through local Principal Investigator	Through local Principal Investigator	
Training of TPI regarding how to perform their role once centre is activated for recruitment	Local Principal Investigator TPI Manual	Local Principal Investigator WHiTE 8 Research Fellow via 1:1 telephone induction TPI manual Induction summary presentation	
Training TPI regarding the WHiTE 8 trial and consenting procedures	Local Principal Investigator	Local Principal Investigator WHiTE 8 Research Fellow via 1:1 telephone induction WHiTE 8 consent flow diagram and protocol provided	
Peer-support of TPI		Monthly contact by WHiTE 8 Research Fellow WHiTE 8 Research Fellow can be contacted by TPI as required by SMS/WhatsApp/Email	
Digital information provided to TPI	TPI Manual	Induction agenda TPI manual and new TPI checklist Induction summary presentation WHiTE 8 consent flow diagram and protocol TPI contact information consent form	
Identifying patients for the trial	Trauma meeting	Trauma meeting	
Confirmation of randomisation	Automated email to recruiting centre		Automated email to recruiting centre Additional personalised email to express gratitude and encourage further recruitment within 72 hours of randomisation

TPI, trainee principal investigator

## Sample selection

As in many SWATs, a power calculation was not undertaken as the number of participating sites is fixed and driven by the needs of the host trial. All WHiTE centres planned to be recruiting to the WHiTE 8 trial will be included, except the centre in which [name] is based. We anticipate a minimum of 20 centres being involved in recruiting. Trial interventions will only be discontinued if the host trial (WHiTE 8 Copal) is discontinued.

## Randomisation

The WHiTE centres will be randomised by minimisation on a rolling basis as sites become activated to one of the four groups to balance key baseline characteristics. Self-reported site feasibility questionnaires completed by the recruitment centres will be used to collect the information required for the minimisation. Minimisation will be based on the following factors:

1. Cluster size (number of intracapsular hip fractures presenting in the previous year, cut at the median <300 or ≥300)2. High vs Low recruiting centres (<9 or ≥9 per month based on previous RCTs run within WHiTE Cohort)3. Co-recruitment to
WHiTE 5 (yes/no) (Another RCT using the same patient population running at a few of the recruitment sites)

This randomisation will be performed using specialist computer software, MinimPy (Saghaei and Saghaei, 2011). This is an open trial and participating sites, the data analyst nor trial team will be blind to allocation.

## Outcomes

The primary outcome is the total number of patients recruited in the first 6 months from a site opening to recruitment to the WHiTE 8 COPAL trial.

The secondary outcomes are: conversion rate from screened population collected monthly from the central recruitment database (coordinated by the Oxford Clinical Trials Research Unit); and the time taken to implement each intervention from commencing recruitment in each centre.

The trainee’s perspective of their role will be collected through the TPI survey (available as
*Extended data*
^7^ at the end of the SWAT in each centre. The Research Fellow will keep a record of the time taken delivering the TPI education intervention and a log of communication for peer-support during the period of the SWAT to inform future implementation.

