## Data analysis

Analysis will be conducted in STATA v15 on an intention-to-treat basis, including all sites in the group they were originally allocated to regardless of deviations based on non-compliance. Statistical significance will be assessed using logistic regression two-sided statistical tests at the 5% significance level. The trial will be reported to CONSORT guidelines, and a flow diagram will present the progression of sites through the trial.

Baseline data relating to the sites (including the minimisation factors) will be summarised for the four groups as randomised and as analysed to assess whether possible loss-to-follow-up has introduced selection bias. Continuous data will be presented using descriptive statistics (e.g., mean, standard deviation, median, minimum, maximum), while categorical data will be given as counts and percentages. No formal statistical comparison of baseline data will be undertaken between the four groups.

The number of participants recruited per site will be summarised. A Poisson regression model, containing the two interventions (Enhanced TPI and Email Nudge) and the minimisation factors (cluster size, and number recruited per month will be included in their continuous form) will be undertaken. Adjusted incidence rate ratios (IRRs) and associated 95% confidence intervals (CIs) will be obtained from this model. The presence of an interaction between the two interventions will also be tested by including an interaction term in the model. 

Feasibility outcomes, such as the time required to run the education intervention and communication time and methods used for the peer support aspect of the intervention, will be reported descriptively.

A data monitoring committee will not be used as this a trial involving recruiters and patient safety will not be affected by conducting this trial. No formal auditing of trial procedure will take place.

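### Conversion from screened patients rests on a post-randomisation denominator, and the loosely worded logistic regression sentence invites a patient-level test of it that ignores centre randomisation

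*Protocol article*

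**What the plan says.** Under Interventions, the design is a 2×2 factorial with "random allocation of the recruiting centre to one of four groups". Sample selection adds: "We anticipate a minimum of 20 centres being involved in recruiting". Randomisation takes place as sites are activated, and the trial is open to sites, analyst and trial team.

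Under Outcomes, "The primary outcome is the total number of patients recruited in the first 6 months from a site opening to recruitment". The first secondary outcome is the "conversion rate from screened population collected monthly from the central recruitment database". The second is the time taken to implement each intervention. The article does not define a screened patient or say who enters one. Table 1 places the identification of patients at the trauma meeting, under both usual practice and the enhanced trainee package.

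Under Data analysis, a general sentence reads: "Statistical significance will be assessed using logistic regression two-sided statistical tests at the 5% significance level". The number recruited then gets its own model: "A Poisson regression model, containing the two interventions (Enhanced TPI and Email Nudge) and the minimisation factors". Delivery time and communication are to be described only. No analysis is assigned to conversion.

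**The concern.** There are two linked difficulties.

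First, the denominator is formed after allocation. The enhanced package trains the people who recruit, and the "personalised email nudges" encourage them to recruit more. If either leads a centre to look harder for patients, the number screened rises. If either leads a centre to log mainly likely recruits, it falls. In both cases conversion changes for reasons other than how well patients are approached and consented. An intervention that succeeds by widening screening could then appear harmful on this outcome.

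Second, the logistic regression sentence has no clear home. The primary outcome is a count with a Poisson model, and implementation time is a duration. Of the primary and two secondary outcomes, only conversion is a proportion, so an analyst following the text could well fit a logistic model to screened patients. Centres, not patients, are randomised, and such a model without a centre term would give p-values that are too small.

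At stake is a secondary result that could contradict the primary one, with apparent significance, in a study intended to inform how later trials recruit.

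**Working it through.** The article gives no sample size, power or error figure for conversion, so there is nothing to reproduce. The only stated error rate is 5%, two-sided.

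**Inputs from the article.** At least 20 centres, hence 20/2 = 10 against 10 for each factorial comparison. The minimisation cut for cluster size is 300 intracapsular fractures per year, or 300/2 = 150 in six months.

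**Assumptions.** Screened per site, m: 150 (every fracture at the cut is screened), 75 or 50. Intracluster correlation (ICC): 0.01, 0.02, 0.05. Conversion of 40% in the simulation. The article supplies none of these.

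**Step 1, direction.** Conversion ratio = recruitment ratio ÷ screened ratio. The comparison site in the illustration has 100 screened and 40 recruited (40.0%); the intervention site recruits 50, so the recruitment ratio is 50/40 = 1.25.

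| Screened, intervention site | Conversion | Conversion ratio |
|---|---|---|
| 110 | 50/110 = 45.5% | 1.25/1.10 = 1.14 |
| 125 | 50/125 = 40.0% | 1.25/1.25 = 1.00 |
| 140 | 50/140 = 35.7% | 1.25/1.40 = 0.89 |

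The sign reverses once the screened ratio exceeds the recruitment ratio.

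**Step 2, size of a patient-level test.** Design effect DE = 1 + (m − 1) × ICC. True two-sided error = 2 × [1 − Φ(1.96/√DE)].

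| m | ICC 0.01 | ICC 0.02 | ICC 0.05 |
|---|---|---|---|
| 50 | DE 1.49, error 0.108 | DE 1.98, error 0.164 | DE 3.45, error 0.291 |
| 75 | DE 1.74, error 0.137 | DE 2.48, error 0.213 | DE 4.70, error 0.366 |
| 150 | DE 2.49, error 0.214 | DE 3.98, error 0.326 | DE 8.45, error 0.500 |

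A beta-binomial simulation under the null (10 against 10 sites, 20,000 runs) agreed with these to within 0.005. With an ICC of zero the error was about 0.05. A t-test on the 20 site proportions held the error at 0.047–0.053 throughout, including at an ICC of 0.10.

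**Step 3, the two together.** Take the 140-screened illustration over 10 against 10 sites: 500/1400 against 400/1000. The odds ratio is (500/900)/(400/600) = 0.83. The standard error of its log is √(1/500 + 1/900 + 1/400 + 1/600) = 0.085, so z = −2.14 and p = 0.033. With mean m = 120, DE is 1 + 119 × 0.02 = 3.38 or 1 + 119 × 0.05 = 6.95. Dividing z by √DE gives p of about 0.25 or 0.42. The patient-level test would report significant harm beside a 25% gain in recruitment; allowing for centre removes that significance.

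**The case against.** The strongest reply is that no analysis of conversion is stated, so none is stated wrongly. The Abstract presents the secondary outcomes as matters of feasibility and logistics, and feasibility outcomes are to be described, with the listed ones given only as examples. On that reading conversion would have no p-value. An extended protocol is cited but not shown, and the handling of clustering for one secondary outcome is a detail an article may leave to it. Where the Data analysis section is specific, it works by site.

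Much of this stands. A reader might infer that the plan assigns logistic regression to conversion, that this is the only named method that could apply, or that clustering will be ignored. The article supports none of these. The sentence is generic, a Poisson model with log(screened) as offset would also serve, and silence about a centre term is not a decision to omit one.

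A reader might also take it as documented that the trained and nudged staff produce the screening counts. The article says only that the data come from a central database coordinated by the trials unit. The identification step is the same under usual practice and the enhanced package, and the nudge follows a randomised patient, not a screening entry. An effect on screening is plausible but not shown.

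Nor is divergence between conversion and recruitment an error in itself: more screening with a lower yield is informative, provided that the screening volume is seen.

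The reply does not remove the post-randomisation denominator, which follows from the outcome's definition and the design. Nor does it excuse a general testing sentence that does not match the Poisson model and that, followed literally, fits only conversion.

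**Conclusion.** The point holds in a limited form. Conversion can move against recruitment whenever screening grows by more than recruitment. If the logistic sentence were applied to screened patients without allowing for centre, the nominal 5% error would be about 11–29% at 50 screened per site and 21–50% at 150, for ICCs of 0.01–0.05. These sizes depend on assumed ICCs and cluster sizes. The figure of 150 is high for many centres, because it supposes that every fracture is screened at a centre on the median cut. The illustrative counts are also assumed.

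It would be wrong to conclude that the trial's main result is compromised. The primary outcome is a site count with no screened denominator, and nothing here touches it. The matter is confined to one secondary outcome and one badly placed sentence, but it is worth correcting because the change is small.

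**What to change.** 1. Remove the logistic regression sentence, or replace it with one that gives only the two-sided 5% level and leaves the model to each outcome.
2. Either report conversion descriptively without a p-value, or analyse it with the centre as the unit. Suitable choices are an overdispersed binomial model on site totals, or a site-count model with a log(screened) offset and overdispersion, with a t reference in either case.
3. Report the number screened per site by group beside conversion, and state that conversion is interpreted only together with screening volume. A short definition of a screened patient would help.

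A further outcome of recruits per previous-year fracture is not needed: the primary model already adjusts for cluster size in continuous form, so it would add little.

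The cost is wider intervals for conversion and one more reported site-level count. The screened counts are already needed to calculate conversion.

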## Ethical issues

The University of York Health Sciences Ethics Committee has approved this study within a trial. Ethics Approval ID: HSRGC/2018/266/C. Substantive protocol amendments will be sought approval through then university ethics committee.

## Trial registration

This SWAT is registered with ISRCTN (
11600053) and is embedded in the WHITE 8 Copal trial (ISRCTN
15606075).

This SWAT is also registered to the SWAT repository store as part of the Northern Ireland Hub for Trials Methodology Research (
SWAT 67).

## Data analysis

Analysis will be conducted in STATA v15 on an intention-to-treat basis, including all sites in the group they were originally allocated to regardless of deviations based on non-compliance. Statistical significance will be assessed using logistic regression two-sided statistical tests at the 5% significance level. The trial will be reported to CONSORT guidelines, and a flow diagram will present the progression of sites through the trial.

Baseline data relating to the sites (including the minimisation factors) will be summarised for the four groups as randomised and as analysed to assess whether possible loss-to-follow-up has introduced selection bias. Continuous data will be presented using descriptive statistics (e.g., mean, standard deviation, median, minimum, maximum), while categorical data will be given as counts and percentages. No formal statistical comparison of baseline data will be undertaken between the four groups.

The number of participants recruited per site will be summarised. A Poisson regression model, containing the two interventions (Enhanced TPI and Email Nudge) and the minimisation factors (cluster size, and number recruited per month will be included in their continuous form) will be undertaken. Adjusted incidence rate ratios (IRRs) and associated 95% confidence intervals (CIs) will be obtained from this model. The presence of an interaction between the two interventions will also be tested by including an interaction term in the model. 

Feasibility outcomes, such as the time required to run the education intervention and communication time and methods used for the peer support aspect of the intervention, will be reported descriptively.

A data monitoring committee will not be used as this a trial involving recruiters and patient safety will not be affected by conducting this trial. No formal auditing of trial procedure will take place.

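### The primary Poisson model makes no allowance for leftover variation between sites: unless that variation is near zero, its 95% intervals are too narrow and its 5% tests reject too often

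*Protocol article*

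**What the plan says.** Centres are the randomised units: the Interventions section describes "random allocation of the recruiting centre to one of four groups". On numbers, Sample selection says "We anticipate a minimum of 20 centres being involved in recruiting". Each centre contributes a single count. The Outcomes section reads: "The primary outcome is the total number of patients recruited in the first 6 months from a site opening to recruitment".

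For the analysis, the Data analysis section names "A Poisson regression model, containing the two interventions (Enhanced TPI and Email Nudge) and the minimisation factors", adding that "cluster size, and number recruited per month will be included in their continuous form". It continues: "Adjusted incidence rate ratios (IRRs) and associated 95% confidence intervals (CIs) will be obtained from this model". The interaction is tested by adding a term to the same model. The abstract also names Poisson regression.

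Nothing in the article mentions overdispersion, scaled or robust standard errors, a negative binomial model or a site random effect. The one sentence on testing reads "Statistical significance will be assessed using logistic regression two-sided statistical tests at the 5% significance level". Logistic regression does not fit a count outcome, so that sentence needs reconciling with the Poisson model, and it does not supply the missing variance rule.

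**The concern.** A Poisson model sets the variance of each site total equal to its mean. Its standard errors therefore depend on how many patients were recruited, not on how much the randomised centres differ. That is valid only if cluster size, past recruitment and WHiTE 5 co-recruitment account for every systematic difference between hospitals. Whatever they leave unexplained is counted as if it were signal.

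Both main effects and the interaction are read from this model. If residual site variation exists, ordinary differences between hospitals can appear as effects of the trainee package or the nudge. The abstract says the results will inform the design of later trials, so a false positive would have consequences.

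**Working it through.** **Inputs from the article.** Two-sided 5% level; 20 sites, so about 10 against 10 for each intervention; one count per site; two interventions and three minimisation factors in the model. Residual degrees of freedom: 20 − (1 + 2 + 3) = 14, or 13 with the interaction.

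**Inputs that are assumed.** The article gives no expected count and no residual CV. Its only recruitment rate is a cut-point: "High vs Low recruiting centres (<9 or ≥9 per month based on previous RCTs run within WHiTE Cohort". Carried over to this host trial, which is itself an assumption, it gives 9 × 6 = 54 per site. I also use 2 and 4 a month (12 and 24 per site). Residual CVs run from 0 to 0.5, and to 0.7 in the simulation. Standard errors are taken to be the Poisson model's own.

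**Formula.** With mean μ and residual CV, a site total has variance μ + (CV·μ)², so the dispersion is φ = 1 + μ·CV². Poisson standard errors are too small by √φ. The true size of a nominal 5% z test is 2 × [1 − Φ(1.96/√φ)].

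**The plan's own figure.** With CV = 0, φ = 1 and the size is 5.0%. The stated level is met if there is no residual variation.

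**With residual variation.** Example at μ = 54, CV = 0.3: φ = 1 + 54 × 0.09 = 5.86, √φ = 2.42, 1.96/2.42 = 0.81, size 41.8%.

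| Residual CV | μ = 12 | μ = 24 | μ = 54 |
|---|---|---|---|
| 0.1 | 6.4% | 7.8% | 11.4% |
| 0.2 | 10.7% | 16.2% | 27.0% |
| 0.3 | 17.4% | 27.0% | 41.8% |
| 0.5 | 32.7% | 45.9% | 60.7% |

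Coverage of the nominal 95% interval is 100% minus these figures. Over CV 0.2 to 0.5 it runs from about 89% down to 39%. The size reaches 15%, three times nominal, at φ of about 1.85, that is, a residual CV of about 0.13 at μ = 54, 0.19 at μ = 24 and 0.27 at μ = 12.

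**Simulation.** 20 sites, balanced random allocation (not minimisation), gamma-Poisson counts under the null, both interventions plus two continuous covariates and one binary covariate in the model, 1,500 replicates per setting. The size is for one intervention main effect.

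| μ, CV | Plain Poisson | Sandwich (HC1), z | Pearson-scaled (floor 1), t on 14 df |
|---|---|---|---|
| 12, 0 | 5.3% | 13.1% | 2.7% |
| 24, 0 | 5.0% | 13.6% | 2.4% |
| 54, 0 | 5.1% | 14.7% | 3.1% |
| 12, 0.3 | 17.4% | 14.5% | 5.1% |
| 24, 0.3 | 28.5% | 15.4% | 6.7% |
| 54, 0.3 | 41.7% | 15.1% | 6.8% |
| 54, 0.5 | 59.9% | 15.1% | 5.1% |

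Across CV 0.2 to 0.7 and all three means, the scaled t test has size 4.5% to 6.8%. The sandwich z test has size 13% to 16% in every setting, including CV 0.

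**Interval width.** By hand at μ = 54, the Poisson standard error of the log rate ratio is √(1/540 + 1/540) = 0.061, so the interval is ×/÷ exp(1.96 × 0.061) = 1.13. At CV 0.3, scaled and with t = 2.145, it is exp(2.145 × 0.061 × 2.42) = 1.37. The simulated medians, which include covariate adjustment, are 1.14 and 1.40. At μ = 24 and CV 0.3 they are 1.22 and 1.45.

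The interaction was not simulated. The same factor √φ applies to its standard error.

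**The case against.** The strongest reply is that this is a condensed article. An extended protocol is listed under Extended data but not shown, an analysis plan may exist, and either could contain a dispersion rule. A Poisson regression with scaled errors is still a Poisson regression, and nothing in the article rules it out. That stands as a limit on what can be known. It does not remove the point: the article names the model and says that the intervals come from it, and followed as written that gives unscaled errors.

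A reader might go further and infer from the table that the intervals will be far too narrow and that the test will reject a true null several times too often. The documents do not support that. They give no residual CV and no expected count, and the cut of 9 a month comes from earlier trials. At CV 0.1, or at CV 0.2 with 12 recruits per site, the size is only 6% to 11%.

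Nor does minimising on size and past recruitment show large residual variation. Those factors are the ones the model adjusts for, two of them in continuous form, and past recruitment may already carry part of what makes one hospital recruit better than another. They show that sites are expected to differ, not how much difference remains.

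Finally, a reader might infer that negative binomial regression is ruled out. It was not checked across this range, and no conclusion is drawn about it.

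**Conclusion.** The point holds in conditional form. As written, the analysis meets its stated 5% level and 95% coverage only if residual between-site variation is near zero, and any such variation errs towards false positives. Under assumed residual CVs of 0.2 to 0.5 and 12 to 54 recruits per site, the true size is about 11% to 61%; at CV 0.1 it is 6% to 11%. The direction follows from the model. The size rests on the assumed CV and count, on about 20 sites, and on the Poisson model's own standard errors being used. It is worth correcting because the plan has no safeguard if the assumption fails and the correction is cheap.

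**What to change.** Keep the log-link Poisson model and the incidence rate ratios. State in the Data analysis section that all standard errors, confidence intervals and tests, for the main effects and the interaction, use the Pearson dispersion scale, floored at 1, with a t reference on the residual degrees of freedom (about 14 for the main-effects model with 20 sites). Report the dispersion estimate. An alternative is a re-randomisation test that re-runs the minimisation in site order; it needs a random element in the minimisation, which the article does not describe. Default sandwich errors with z tests are not enough with about 20 sites. Replace the reference to logistic regression for this outcome.

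Fix the rule before site totals are compared by group: the Randomisation section says that the analyst and trial team are not blinded, so a later choice of error structure would be hard to defend.

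The cost is a sentence or two and one model option, with no new data. Intervals widen, for example from ×/÷1.14 to ×/÷1.40 at 54 recruits per site and CV 0.3. If there is truly no overdispersion, the test is somewhat conservative, with a size of about 2% to 3%.
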